|------------------------------------------------------|---------------------------|---------------------------------------------------------------------------------------------------------------------------------------------------------------------------------------------------------------------------------------------------------------------------------------------------------------------------------------------------------------------------------------------------------------------------------------------------------------------------------------------------------|--------------------------------------------|
|                                                      |                           | for detecting depression, supporting its clinical utility (Osman et al., 2008).                                                                                                                                                                                                                                                                                                                                                                                                                         |                                            |
| Beck Hopelessness Scale (BHS)                        |                           | Severity of hopelessness will be assessed with the 20-item BHS (Beck & Steer, 1988; Beck, Weissman, Lester, & Trexler, 1974). The scale questions are presented in a true-false format. This scale was designed to assess the degree to which a person has negative future expectancies. Examinations of reliability have demonstrated high internal consistency (e.g., Kuder-Richardson estimate = .93) and adequate test-retest reliability (Beck & Steer, 1988; Katz, Katz, & Shaw, 1999).           | Baseline, W4, W8, W12, W24, W52, W78, W104 |
| Clinical Global Impression severity subscale (CGI-S) | Clinical improvement      | Clinical improvement will be assessed with the Clinical Global Impression severity subscale (CGI-S), which provides a reliable and valid summary measure of a participant illness that takes into account the participant history, psychosocial circumstances, symptoms, behavior, and functional impairment (Guy, 1976). The CGI S evaluates the severity of psychopathology on a scale of 1 (normal, not at all ill) to 7.                                                                            | Baseline, W24, W52, W78, W104              |

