| Clinical Global Impression change subscale (CGI-C)   | Clinical improvement      | Clinical improvement will also be assessed with the Clinical Global Impression change subscale (CGI-C). It assesses how much the participant's illness has improved or worsened relative to their baseline state at the beginning of the intervention on a scale ranging from 1 (very much improved) to 8 (very much worse).                                                                                                                                                                            | W12, W24, W52, W78, W104                   |
| Mechanisms of Action                          |                           |                                                                                                                                                                                                                                                                                                                                                                                                                                                                                                         |                                            |
| Monetary Choice Questionnaire (MCQ)                  | Impulsive decision making | Impulsive decision making will be assessed using the Monetary Choice Questionnaire (MCQ), a self-report questionnaire that presents a series of 27 monetary choices, each of which includes a smaller, immediate monetary reward and a larger, delayed monetary reward (Kirby et al., 2019). Higher values indicate a preference for immediate rewards and impulsivity. MCQ is temporally stable and has been shown to be associated with suicidal behaviors (Dombrovski et al., 2011, 2012).           | Baseline, W12, W24, W52, W78               |
| Cognitive Emotion Regulation Questionnaire (CERQ)    | Emotion regulation        | Emotion regulation will be assessed using the Cognitive Emotion Regulation Questionnaire (CERQ) self-report questionnaire that assesses a range of psychological strategies used in response to emotionally threatening or stressful events (e.g., self-blame, rumination, positive reappraisal). The CERQ is a reliable and valid measure of emotion regulation, and its subscales correlate with emotional distress and psychopathology in the expected directions (Garnefski, N., Kraaij, V., 2007). | Baseline, W12, W24, W52, W78               |

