#### **11.1.4 Group Sequential Design for Suicide Attempts**

Although the dropouts will not provide the clinical interview information at study end, it will be possible to review hospital records to obtain information regarding suicide attempts by participants (this will be confirmed during informed consent). We will randomize 196 participants to the (Aviva) treatment group and 195 participants to the active control (sham) group and expect to have suicide attempt data for 100% of these participants. We investigated several reasonable variations of the group sequential design and determined that the following is most reasonable. We will test at the 0.025 significance-level (one-sided). The group sequential design has 3 interim sequential tests (4 total looks including final analysis). The looks will occur when 60%, 75%, 90% and 100% of the expected events (i.e., suicide attempts) have occurred. The O'Brien-Fleming spending function is used to determine the effectiveness test boundary. The group sequential design boundaries (on a z scale) are presented in Attachment C.

The power of this GSD is 90%.

Survival analyses will be conducted using the log-rank test for the effectiveness of the intervention on the time to the first suicide attempt after randomization while controlling for censoring effects due to the differential length of follow-up or the completion of follow-up without a suicide attempt. Time to suicide attempt will be measured by calculating the total number of days from enrollment to the first suicide attempt. For participants without a suicide attempt, the total number of days since enrollment to the last assessment will be calculated.

While every effort will be made to track suicide attempts (SA), there may be some missing data. Consistent with standard statistical procedures, missing data are included in the time-to-event analysis as censored observations, with the censoring time at the last contact time with the patient (Friedman et al., 2015).

Estimates of participants making at least 1 subsequent suicide attempt before study end and reattempt-free probabilities at any time point will be derived by the Kaplan-Meier method. The

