### **11.2.2 Suicidal Ideation**

Effect size will be used as a measure of minimally clinically significant difference (MCID). This study has been designed to detect an effect size of 0.50 for suicidal ideation (assessed through the SSI), which is both a moderate effect size and a clinically significant amount. To calculate this expected effect size, the standard deviations presented in research that used the same suicide prevention techniques proposed to implement with Aviva (Bryan et al. 2017) were reviewed. The clinical significance of the findings of studies using the proposed techniques (Brown et al., 2005, Bryan et al., 2017, Rudd et al., 2015) is evidenced by the adoption of these techniques by the Joint Commission (The Joint Commission, 2016) and the U.S. Department of Veterans Affairs (U.S. Department of Veterans Affairs, 2008).

To support the effectiveness of Aviva for SI, it will be beneficial to demonstrate what constitutes a clinically meaningful within-patient change in scores (i.e., improvement threshold), from the patient perspective, in addition to an MCID across all patients. To estimate a clinically meaningful within-patient change, the following scales will be included to support a clinically meaningful within-patient change analysis (an improvement score of 1 unit on the CGI-C scale), and aim to achieve statistically significant and clinically meaningful differences in a responder analysis between the treatment and control groups for the two scales identified below:

- Clinician Global Impression of Severity (CGI-S) administered at baseline, 24 weeks and at study end
- Clinician Global Impression of Change (CGI-C) administered at 24 weeks and at study end

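### The CGI-C is described as a 1-to-8 change scale with no midpoint and no stated 'no change' score, yet a 1-unit improvement on it defines meaningful change

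*Protocol*

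**What the plan says.** The assessment table in protocol section 7.1 describes the CGI-C as two-directional: "It assesses how much the participant's illness has improved or worsened relative to their baseline state at the beginning of the intervention". It gives the range as "on a scale ranging from 1 (very much improved) to 8 (very much worse". Only the two end scores carry labels; scores 2 to 7 are not described, and no score is named as unchanged.

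The entry above it gives the companion severity scale seven points: "The CGI S evaluates the severity of psychopathology on a scale of 1 (normal, not at all ill) to 7".

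Section 11.2.2 puts the CGI-C to use in two ways. It sets the threshold for a meaningful within-patient change as "an improvement score of 1 unit on the CGI-C scale", and for the CGI-S and CGI-C it states that the trial will "aim to achieve statistically significant and clinically meaningful differences in a responder analysis between the treatment and control groups". It does not name the score from which the one unit is counted.

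**The concern.** A rating that runs from one extreme of improvement to the opposite extreme of worsening needs a place for the patient who has not changed. On an evenly spaced scale with an even number of points, no central score is available for that patient.

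This would be a small slip in wording if nothing rested on the neutral point, but section 11.2.2 rests on it. The CGI-C is itself a change score, so a one-unit improvement cannot be calculated by subtracting a baseline value. It can only mean one step better than unchanged. If the unchanged score is undefined, so is the responder, and so is the threshold meant to help interpret change in the SSI.

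The range also matters before any analysis plan comes into play. A cut-off can be fixed later in a statistical analysis plan. A neutral response that raters were never offered cannot be recovered from the data.

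**Working it through.** The protocol gives no expected rate, power or sample size for the CGI-C, so there is no planned figure to reproduce. The check has three steps.

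**1. Midpoint of the scale.** For a scale scored 1 to k, the midpoint is (1 + k)/2.
- k = 8 (CGI-C, section 7.1): (1 + 8)/2 = 4.5, which is not a score. There are four points on each side.
- k = 7 (for comparison, an odd number of points): (1 + 7)/2 = 4, which is a score.

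**2. Where one unit of improvement falls.** Table 1 schedules the CGI-C only after baseline, from week 24. Section 7.1 lists it from week 12. Neither gives a baseline rating. Lower scores are better, so the responder rule depends on the assumed neutral score:
- neutral at 5: response is 4 or lower;
- neutral at 4: response is 3 or lower;
- neutral at 4.5: one category better is 4 or lower, but one full unit is 3.5, which means 3 or lower.

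The text of 11.2.2 fits either cut-off.

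**3. Effect of splitting unchanged participants.** Let I be the improved share and U the unchanged share, with subscripts A for Aviva and S for sham. Let f be the share of unchanged participants who are scored 4, taken as equal in both arms because assessors are blinded. If the cut-off counts 4 as response, the responder rate in an arm is I + fU, and the difference is

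(I_A − I_S) + f(U_A − U_S).

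All shares below are assumptions, with f = 0.5.

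| Improved A / S | Unchanged A / S | Difference, unchanged kept separate | Responders A / S after splitting | Difference after splitting |
|---|---|---|---|---|
| 50% / 35% | 35% / 35% | 15 points | 67.5% / 52.5% | 15 points |
| 50% / 35% | 35% / 40% | 15 points | 67.5% / 55% | 12.5 points |
| 50% / 30% | 30% / 50% | 20 points | 65% / 55% | 10 points |
| 45% / 35% | 40% / 30% | 10 points | 65% / 50% | 15 points |

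The difference stays, falls or rises according to whether the unchanged share in the Aviva arm equals, is below or is above that in the sham arm. The rate within each arm moves whenever f is above zero. In the first row the sham rate is 35% at f = 0 and 35% + 35% = 70% at f = 1. If the cut-off is 3 or lower, participants scored 4 are not responders, and splitting the unchanged between 4 and 5 does not alter the comparison.

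**The case against.** The strongest objection is that the protocol never says the scale lacks a 'no change' category. Scores 2 to 7 are unlabelled, so a 'no change' label could sit off-centre at 4 or 5, or the 8 could be a typing error. This stands. A reader might infer that 'no change' is certainly absent and that unchanged participants must be scored as better or worse, but the text does not establish either. The seven-point CGI-S does not settle the matter, because it measures severity in one direction.

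A reader might also infer that the responder comparison is diluted. There is a plausible route to that: writing W for the worsened share, the difference equals (1 − f)(I_A − I_S) + f(W_S − W_A), so it shrinks if the app raises improvement by more than it lowers worsening. But the protocol gives no shares, the working shows cases with no loss and with a gain, and the effect disappears under the stricter cut-off. Dilution is one possibility among several.

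Finally, the exact responder rule may properly be left to the statistical analysis plan, and the eCRF, which may already carry a 'no change' option, is not at hand. Both points are fair. They do not answer the stated range, which defines how the rating is collected. Section 11.4, under staff training, also undertakes to give clear definitions of the variables assessed.

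**Conclusion.** The point holds in limited form. As stated, the CGI-C range has no midpoint and no identified neutral score, while section 11.2.2 relies on a unit of improvement that needs one. Either the range is wrong, or the instrument needs its neutral category spelled out.

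If the scale is built as written and evenly spaced, responder rates in both arms and the meaningful-change threshold would depend on how raters place unchanged participants. The between-arm difference could move either way or not at all, depending on the unchanged share in each arm and on the cut-off. No single size can be given, because every share used above is an assumption.

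The reach is small. The CGI-C is listed among other evaluations in the synopsis and serves to interpret the SSI. The primary log-rank test, the sample size of 391 and the SSI model are untouched.

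**What to change.** - In section 7.1, correct the CGI-C range to an odd number of points with an explicit 'no change' midpoint, and print the label for every category.
- Check that the eCRF option list matches, before ratings are collected with it.
- In section 11.2.2, define the CGI-C responder by label: at least one category better than 'no change'.
- While editing, reconcile the first CGI-C visit, which is week 12 in section 7.1 but week 24 in Table 1 and section 11.2.2.

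The cost is a line in 7.1, a sentence in 11.2.2 and a check of one option list. If the eCRF already offers 'no change', only the protocol text changes. The sample size and the primary analysis need no revision.

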## 7.2. INFORMED CONSENT

The participant must personally sign and date the latest approved version of the informed consent form before any study specific procedures are performed. Written and verbal versions of the informed consent will be presented to the participants detailing no less than: the exact nature of the study; the implications and constraints of the protocol; the known side effects and any risks involved in taking part. It will be clearly stated that the participant is free to withdraw from the study at any time for any reason without prejudice to future care, and with no obligation to give the reason for withdrawal.

The participant will be allowed as much time as needed to consider the information, and the opportunity to question the PI, his/her General Practitioner (GP) or other independent parties to decide whether they will participate in the study. Written consent will then be obtained by means of a dated signature of the participant and a dated signature of the person who presented and obtained the informed consent. The person who obtained the consent must be suitably qualified and experienced and have been authorized to do so by the PI. A copy of the signed Informed Consent will be given to the participant. The original signed form will be retained at the study site.

## 7.3 SCREENING AND ELIGIBILITY ASSESSMENT

Everyday the PI or designee will check with hospital staff to see if new potential participant(s) have been admitted. Patients will be told about the opportunity to participate in the study and informed by the research therapists about the voluntary nature of their participation and that their data will remain confidential. Once the patient agrees to participate, the PI will review the patient's medical history and psychological evaluation with the patient and gather additional information to determine whether the patient meets eligibility criteria. After informed consent is given, research therapists will administer a structured clinical interview focused on suicide attempt history.

Prior to enrollment, the following information will be collected:

- Demographic Information
- Medical History
- Concomitant Medications/psychotherapy

Following enrollment, participants will receive instructions on how to install the app on their phone.

## 7.4 PARTICIPANT ENROLLMENT

To preserve participant blinding, participants will be informed that they will be assigned to "one of two digital interventions." Participants will be informed that both interventions include some combination of supportive listening, education about crisis services, software services and referrals to treatment services. Once the patient agrees to participate, the PI will review the patient's medical history and psychological evaluation with the patient and gather additional information to determine whether the patient meets eligibility criteria. The site PI will obtain informed consent from participants using procedures that will be Internal Review Board (IRB) approved. After informed consent is given, research therapists will administer a structured clinical interview focused on suicide attempt history. Upon completion, the research therapist will execute a randomization procedure and the participant will be randomized to the Aviva + TAU or sham +

TAU group (See Section 7.5). Following randomization, participants in both groups will receive an access (SMS) link and instructions on how to install the Aviva or sham apps on their phone. The app is to be downloaded before the end of the study visit.

### 7.5 RANDOMIZATION CRITERIA

Participants who meet the eligibility criteria will be assigned a participant number and will then be randomly assigned to the Aviva + TAU or sham + TAU groups. A computerized modified minimization randomization procedure within the electronic Case Report Forms (eCRFs) will be used. Eligible participants will be randomized based on study site, sex, race/ethnicity and whether they have had no attempts, single attempts or multiple suicide attempts. This adaptive randomization method has been shown to be superior to stratified randomization in producing balance for separate prognostic variables, particularly when the number of strata is large compared with the number of subjects. Once the participant is randomized the site staff will make sure that the participant has properly loaded Aviva **or** sham app onto his/her phone. The PI or designee will confirm that the app has been downloaded and, if the participant is having difficulty, assist them beginning the onboarding session.

### 7.6 CONCOMITANT MEDICATIONS/PSYCHOTHERAPY

All concomitant medications will be recorded at the Baseline Visit. The use of ongoing and any new medications will then be noted at each following study visit. All medication use will be captured by research assessors from participants in follow-up visits in the source documents and on the appropriate eCRF page. The following information will be recorded for each medication: name, indication, dose, frequency, start date, end date. Participation in outpatient psychotherapy will also be recorded with the Cornell Services Index (CSI). Additionally we will collect data from the psychotherapy providers about attendance, medication, and anything related to the patient safety.

### 7.7 RETENTION METHODS

The researcher staff will collect contact information for participants, including participant's email addresses, telephone numbers and addresses for home and employment locations as well as contact information of their TAU provider. The study staff will also collect contact information (telephone number and email) for two individuals that the participant identifies as people who will always know how to reach them. Study staff will also ask study participants to provide contact information for their outpatient mental health care provider and then verify that contact information. Detailed information will also be collected about other community contacts. Thus, if participants cannot be contacted, family, friends, clergy, probation officers, and mental health workers will be contacted by research staff with permission from the participants. These contacts will be confirmed within 24 hours of each assessment. Study staff will also follow up with outpatient mental health care providers using the same cadence as study participants' follow up visits: at weeks 4, 8, 12, 24, 52, 78 and 104. Participants will be assured of confidentiality when they share this data (and throughout the study). At enrollment, site staff will ask participants to report their preferred method of communication (i.e., email, text message, or phone call) in order to use the notification strategy that they're most likely to pay attention to. The app will collect participant usage metrics with the goal of improving participants' adherence to this recommended treatment. If participants miss a session, these metrics will allow Aviva to send prompts to participants until they initiate or reschedule a session. Messages will be sent to participants, via their preferred method of communication, which will include reminders to engage with the study, motivating statements (e.g., Great job!) for participating and encrypted emails to acknowledge important milestones in their participation. When participants are not attending outpatient mental health

sessions the Sponsor will send participants correspondence, based on the participants preferred method of contact, to remind them of their treatment plan.

#### 7.8 STUDY INTERVENTION COMPLIANCE

Compliance will be measured with weekly reports by the study sponsor. The study sites will be notified of participant non-compliance.

